**Figure 1 figure1:**
[figure not shown]
Research framework. GEP: gerontechnology empowerment program.

### Research Instrument

The data collection process for this study will involve the use of structured questionnaires in both English and Kannada. The questionnaire will cover the following key areas: demographic information—participants will provide essential demographic details, including age, gender, educational qualifications, income range, the presence of chronic diseases, and the type of smartphone they use; awareness and use level of mobile apps for iADLs—this section will measure older adults’ awareness and usage level regarding various mobile apps designed to address the 8 components of iADL; and motivational factors and barriers—this portion of the questionnaire will explore the motivational factors and barriers influencing older adults’ adoption and use of mobile apps. It will encompass dimensions such as performance expectancy, social influence, facilitating condition, effort expectancy, technology anxiety, awareness factors, and resistance to change.

Collecting data in both English and Kannada ensures that participants can comfortably respond in their preferred language, facilitating accurate and comprehensive data collection from a diverse group of older adults.

### Instrument Validity and Reliability

The instruments used in this study underwent a rigorous validation process. Experts from various fields, including health care, social studies, information technology, and the older adults’ welfare department, were engaged in the validation process. These experts were presented with a clear understanding of the study’s objectives and its blueprint. The reliability was established among 20 participants and evaluated through the test-retest method, ensuring consistent responses. Additionally, Cronbach α, a statistical measure of internal consistency, was used to assess the reliability of awareness and usage level on mobile apps for iADLs (*r*=88) and motivational factors and barriers (*r*=73) instruments. Furthermore, a pilot study was conducted among 10 participants to assess the study’s feasibility and accuracy in January 2023.

### Data Collection Plan

The study is in progress by visiting older adults’ welfare organizations after obtaining prior approval. In phase 1, participants will receive a subject information sheet in both Kannada and English to explain the study details. Data will be collected using a structured questionnaire, with participants’ consent, to assess their awareness and the factors influencing the use of mobile apps for iADLs. In phase 2, cluster randomization will be used to select older adults for the experimental or control groups. The GEP will be administered to the experimental group. The effectiveness of the GEP will be assessed through measurements taken before and after its implementation.

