**Methods:**

This research uses a quantitative approach divided into 2 distinct phases. In phase 1, we conduct a descriptive survey to assess the level of awareness and use of mobile apps for iADLs and identify the factors that influence the use of such apps among older adults. To ensure clarity and comprehension among participants, we provide them with a subject information sheet in both Kannada and English. The data collected during this phase enable us to gain insights into awareness levels, use patterns, and factors that shape older adults’ use of apps for iADLs. The results serve as the foundation for designing the GEP. In phase 2, a cluster randomization method will be used to select older adults aged 60 to 75 years in Udupi district, Karnataka, India, who are active smartphone users. These participants will be divided into 2 groups: the experimental and the control groups. The experimental group will join the GEP. The sample size for phase 1 is 554, and phase 2 is 50. To assess the effectiveness of this program, we will measure the outcomes before and after its implementation using the same assessment tools used in phase 1.

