## Methods

### Research Design

The research design for phase 1 is cross-sectional descriptive research, and phase 2 is a cluster randomized control trial. The Indian Council of Medical Research Guidelines for Extramural Research was adopted to prepare the funding proposal [24].

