### Sample Size

Sample size calculations were performed separately for phase 1 and phase 2 of the study. For phase 1, a sample size of 369 participants was estimated based on proportion values. This sample size was then adjusted by a design effect of 1.5 to account for potential clustering or stratification, resulting in a required sample size of 554 participants. In phase 2, the focus was on comparing 2 proportions. To ensure the study’s robustness in the face of potential dropouts (estimated at 20%), an initial sample size of 31 participants was calculated for each group. This initial size was adjusted by a design effect of 1.5 to consider the study’s specific design characteristics, yielding a total required sample size of 46 participants per group, rounded up to 50 participants per group.

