### Statistical Analysis

#### Plan for Data Analysis

To evaluate the awareness and use of mobile apps among older adults, frequency and percentage distribution will be used as a statistical method. A combination of statistical techniques will be used to analyze the influencing factors, including descriptive statistics to provide a summary of the data and logistic regression to model the relationship between the influencing factors and mobile app use. A sequence of statistical tests will be applied to measure the effectiveness of the GEP. These tests include repeated measures ANOVA, 2-tailed *t* test, Mann-Whitney *U* test, Wilcoxon signed rank test, and *χ*^2^ test. These tests will help assess the impact and changes brought about by the GEP on various outcome measures.

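### The GEP effectiveness tests mix a within-arm paired test with between-arm tests; no between-arm contrast is said to decide, and none is adjusted for baseline

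*Protocol article*

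**What the plan says.** The Research Design section states that "phase 2 is a cluster randomized control trial". The Data Collection Plan adds that "cluster randomization will be used to select older adults for the experimental or control groups", and that the GEP goes to the experimental group. It then says: "The effectiveness of the GEP will be assessed through measurements taken before and after its implementation". The abstract's Methods paragraph says much the same: "we will measure the outcomes before and after its implementation using the same assessment tools used in phase 1". Neither sentence names a contrast between arms.

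The Plan for Data Analysis says: "A sequence of statistical tests will be applied to measure the effectiveness of the GEP". It continues "These tests include repeated measures ANOVA, 2-tailed" and goes on to the *t* test, the Mann-Whitney *U* test, the "Wilcoxon signed rank test" and the chi-square test. None is marked as decisive. The article does not say whether the *t* test is paired or independent, whether arm is a factor in the ANOVA, or whether the two-group tests use post-programme scores or changes. In the Sample Size section, phase 2 is planned on the basis that "the focus was on comparing 2 proportions".

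**The concern.** In a two-arm trial with one measurement before and one after, the signed rank test asks whether scores moved within an arm. It cannot separate the programme's effect from anything else that moves scores over the same period. Here participants answer the same awareness and use questionnaire twice, and being asked about apps may itself raise awareness. Some common rise in both arms is therefore plausible, although the article gives no figure for it. The article lists the paired test as a measure of effectiveness and does not say that a between-arm result takes precedence. A significant change in the experimental arm alone could therefore be reported, within the plan as written, as evidence that the GEP works.

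The second issue is precision. Each participant's baseline value is collected, but no listed method uses it as a covariate in the comparison of arms. With 50 participants per group, before any loss and before the effect of clustering, that precision is worth having.

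**Working it through.** **The plan's own figure.** The Sample Size section starts from 31 per group and applies a design effect of 1.5: 31 × 1.5 = 46.5. The article gives 46, rounded up to 50 per group, so the step reproduces apart from truncation. The 31 itself cannot be reproduced, because the two proportions, alpha and power are not given. I use 50 per group and, with the stated 20% dropout, 50 × (1 − 0.20) = 40 completers per arm.

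**Assumptions not in the documents.** Pre-post correlation ρ of 0.3, 0.5 or 0.7; equal variance before and after; a common shift of 0 to 0.5 SD in both arms; for power, an effect of 0.5 SD and two-sided alpha of 0.05. Scores are treated as continuous.

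**1. Within-arm reading when the GEP has no effect.** The SD of an individual change is √(2(1 − ρ)), which is 1.0 at ρ = 0.5. I took 40 completers per arm, ρ = 0.5, independent participants, the same shift in both arms and a signed rank test in the experimental arm at 5%. In a simulation of 3,000 trials:

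| Common shift (SD) | Significant in GEP arm |
|---|---|
| 0 | 5% |
| 0.2 | 22% |
| 0.3 | 43% |
| 0.5 | 86% |

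A separate run of 5,000 trials gave 5%, 23%, 45% and 86%, so the figures are good to about two percentage points. In that run the pattern of significance in the GEP arm but not in the control arm appeared in 17% of trials at 0.2 SD, 25% at 0.3 SD and 12% at 0.5 SD. Comparing the two within-arm *p*-values is therefore no safeguard.

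**2. Precision of the valid between-arm options.** Variance of the arm difference, relative to comparing post-programme scores only:

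- change score (the group-by-time term with two time points): 2(1 − ρ)
- adjustment for baseline (ANCOVA): 1 − ρ²
- ratio of ANCOVA to change score: (1 − ρ²) / (2(1 − ρ)) = (1 + ρ)/2

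| ρ | Post only | Change | ANCOVA | ANCOVA / change | Reduction |
|---|---|---|---|---|---|
| 0.3 | 1 | 1.40 | 0.91 | 0.65 | 35% |
| 0.5 | 1 | 1.00 | 0.75 | 0.75 | 25% |
| 0.7 | 1 | 0.60 | 0.51 | 0.85 | 15% |

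At ρ = 0.5 the gain equals 1/0.75 = 1.33, or one third more participants.

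**3. What this means for power.** The effective size is 50/1.5 = 33.3 per arm, and power = Φ(0.5 / √(2v/33.3) − 1.96), with v the relative variance above.

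| ρ | Post only | Change / group-by-time | ANCOVA |
|---|---|---|---|
| 0.3 | 53% | 41% | 57% |
| 0.5 | 53% | 53% | 65% |
| 0.7 | 53% | 75% | 82% |

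The variance formulas are individual-level. Applying the same design effect of 1.5 to each method is a simplification, and the gain for a binary outcome would differ.

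**The case against.** The strongest reply is that the article does set up a comparison of arms. The design is a randomised trial with a control group, the sample size rests on two proportions with a size calculated for each group, and the before-and-after sentence stands in a data collection section, where it may say only when outcomes are measured. Repeated measures ANOVA heads the list. With arm as a factor, its group-by-time term compares arms, uses every baseline value and subtracts baseline differences. The Mann-Whitney, chi-square and independent *t* tests also compare groups. The choice of decisive test and of covariates is commonly left to an analysis plan, which is not shown. ANCOVA over change scores is a matter of precision, since under randomisation both target the same average effect.

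Most of this stands, and it rules out three stronger readings. A reader might infer that within-arm tests replace the comparison of arms; the text does not say so. A reader might infer that the baseline data are wasted or that imbalance would go uncorrected; the group-by-time term would use them, only less efficiently. A reader might add that few organisations will be randomised and that chance imbalance is therefore likely; the article gives no number of clusters and speaks only of various organisations.

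What remains is not merely an omission. The article itself lists a paired test as a measure of effectiveness, and no unseen document removes that statement. The simulated percentages show a hazard that the text permits; they are not the trial's error rate, because no within-arm decision rule is stated.

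**Conclusion.** The point holds as one of interpretation and efficiency. The Plan for Data Analysis offers a within-arm paired test and between-arm tests side by side as measures of GEP effectiveness, does not say that the between-arm result decides, and names no baseline-adjusted comparison.

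If a within-arm result were taken as effectiveness, a useless programme would appear to work in about 43% of trials at a common shift of 0.3 SD and in 86% at 0.5 SD. This is conditional on 40 completers per arm, a correlation of 0.5 and independent participants. Against the valid group-by-time comparison, baseline adjustment saves 35%, 25% or 15% of the variance at correlations of 0.3, 0.5 or 0.7. The shifts and correlations are assumptions, and the planned sample size is unaffected. None of this proves that the plan leaves out the control arm.

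**What to change.** In the Plan for Data Analysis, state that effectiveness is the between-arm difference in the post-programme outcome, estimated in a model that includes the participant's own baseline value and accounts for clusters. For a binary outcome, use the corresponding model with the baseline response as covariate. Report changes within each arm descriptively, without using them as evidence of effectiveness, and take the Wilcoxon signed rank test out of the list that serves that purpose. Align the before-and-after sentences in the Data Collection Plan and the abstract, so that they describe measurement times and refer to the between-arm contrast for the conclusion.

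The cost is wording in the protocol and analysis plan. The baseline measurement is already planned, no participants or visits are added, and the Results section describes phase 2 as still to commence, so the change can be made before any phase 2 outcome is seen.

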### Statistical Analysis

#### Plan for Data Analysis

To evaluate the awareness and use of mobile apps among older adults, frequency and percentage distribution will be used as a statistical method. A combination of statistical techniques will be used to analyze the influencing factors, including descriptive statistics to provide a summary of the data and logistic regression to model the relationship between the influencing factors and mobile app use. A sequence of statistical tests will be applied to measure the effectiveness of the GEP. These tests include repeated measures ANOVA, 2-tailed *t* test, Mann-Whitney *U* test, Wilcoxon signed rank test, and *χ*^2^ test. These tests will help assess the impact and changes brought about by the GEP on various outcome measures.

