### Recruitment

This study is structured around a 2-phase research design (Figure 1). The sample was selected purposively from welfare associations of the Udupi district. Phase 1 was initiated after the ethics and Clinical Trials Registry - India approval. For the study’s second phase, the sample will be randomly allocated to experimental and control groups from various welfare organizations of the Udupi district. We have planned to use the clustered randomization process to select participants based on the study’s eligibility criteria.

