#### Develop and Determine the Effectiveness of a GEP

The GEP will be a comprehensive intervention designed to facilitate the use of smartphone apps for iADLs. The development of GEP will be based on the findings from the study’s first phase, incorporating insights from experts in health care, mobile technology, and older adults’ welfare departments or organizations. The structure of the GEP program will encompass the following components: information and features—detailed information about smartphone apps relevant to iADLs, including their features and functionalities; installation procedures—step-by-step guidance on installing and setting up these smartphone apps; general awareness—fundamentals of smartphone use and general awareness regarding its capabilities; security awareness—guidelines on ensuring smartphone security and safe use; dos and don’ts—best practices and precautions for effective and responsible smartphone use; operation manuals—manuals provide instructions on operating specific smartphone apps for iADLs. The training program will be conducted through 8 sessions, each lasting 3 hours. These sessions will incorporate hands-on training using audiovisual facilities to enhance participants’ understanding and practical skills in using smartphone apps effectively for iADLs.

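### Phase 1 is enlarged by a design effect of 1.5, but no analysis named for it accounts for welfare association membership

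*Protocol article*

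**What the plan says.** Under Sample Size, the protocol article states that for phase 1 "a sample size of 369 participants was estimated based on proportion values". It continues: "This sample size was then adjusted by a design effect of 1.5 to account for potential clustering or stratification". The target after this step is 554. The section gives no proportion, precision or confidence level for the 369, and it does not name the cluster unit.

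The Participants section limits the study to smartphone users aged 60 to 75 who are affiliated with welfare organizations. Recruitment says: "The sample was selected purposively from welfare associations of the Udupi district". The Data Collection Plan describes visits to those organizations.

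Under Plan for Data Analysis, for awareness and use, "frequency and percentage distribution will be used as a statistical method". For the influencing factors it names descriptive statistics and "logistic regression to model the relationship between the influencing factors and mobile app use". It mentions no cluster-robust variance, generalized estimating equations (GEE), random effect or survey weighting.

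**The concern.** A design effect in the sample size says that 554 respondents are expected to carry less information than 554 independent people. The analysis has to reflect the same belief. If it does not, the 185 extra participants (554 − 369) count as full independent information and the standard errors come out too small.

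The source of clustering is easy to see. People reached through the same association share meetings, helpers and local conditions, and may resemble one another in app awareness and use. Association is therefore the natural unit to account for, although the protocol does not say so.

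The regression is where this matters. It is meant to identify which factors influence app use, and the programme is to draw on it: "The development of GEP will be based on the findings from the study’s first phase, incorporating insights from experts". Standard errors that are too small make a factor look influential more often than the nominal level allows.

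**Working it through.** **Inputs.** From Sample Size: base 369, design effect 1.5, final 554. From Research Instrument: seven motivational or barrier dimensions, and six demographic items (age, gender, education, income, chronic disease, smartphone type). Assumed, because the article does not give them: two-sided 5% level, the proportion and precision behind 369, and the intracluster correlation (ICC) of each factor.

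**1. The protocol's own figure.** 369 × 1.5 = 553.5, rounded up to 554. It reproduces.

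**2. Where 369 could come from.** 1.96² × 0.40 × 0.60 / 0.05² = 368.8, rounded up to 369, so p = 0.40 (or 0.60) with ±5 points fits. The fit is not unique: p = 0.50 with ±5 points and a finite population of 9,000 gives 368.5, also rounded up to 369. Only the half-widths in step 4 depend on p.

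**3. Standard error of a proportion.** Effective sample size = 554 / 1.5 = 369. The correct standard error is √1.5 = 1.22 times the one that ignores clustering.

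**4. Any interval reported for a percentage.**
- Ignoring the design effect, at p = 0.40: 1.96 × √(0.24 / 554) = 4.1 points.
- Allowing for it: 4.1 × 1.22 = 5.0 points.
- At p = 0.50 the two are 4.2 and 5.1 points.
- Actual error of a nominal 5% procedure: 2 × [1 − Φ(1.96 / √1.5)] = 2 × [1 − Φ(1.600)] = 11.0%. A nominal 95% interval therefore covers 89.0%.

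**5. Tests in the logistic regression.** The design effect for a coefficient also depends on how far the factor itself clusters. As an approximation, D = 1 + (m − 1) × outcome ICC × factor ICC, where m is the number of respondents per association. Setting (m − 1) × outcome ICC = 0.5, as the 1.5 implies, gives D = 1 + 0.5 × factor ICC.

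| Assumed factor ICC | D | Actual error of a nominal 5% test |
|---|---|---|
| 0 | 1.00 | 5.0% |
| 0.1 | 1.05 | 5.6% |
| 0.3 | 1.15 | 6.8% |
| 1 (constant within association) | 1.50 | 11.0% |

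**6. Expected false flags.** Suppose all 13 items enter as single factors and none has a true effect. The nominal expectation is 13 × 0.05 = 0.65. At factor ICC 0.1 it is 13 × 0.0558 = 0.73, and at 0.3 it is 13 × 0.0676 = 0.88. If all 13 were constant within associations it would be 13 × 0.1095 = 1.42. That last figure is a ceiling that these items cannot reach, since age, gender and personal attitudes vary within an association.

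**The case against.** The strongest reply is that the gap is inferred from silence. The text says logistic regression. It does not say that respondents are treated as independent, and such a model can be fitted with clustered standard errors. An article condenses its protocol, and the variance estimator is a detail that often sits elsewhere. This stands to the extent that a reader might infer that phase 1 is planned as a simple random sample. The article does not say that. What remains is that the article states the design effect for both phases, calls phase 2 a cluster randomized trial, and names no clustered method for either. That makes the unadjusted reading plausible enough to need closing.

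Three stronger readings are also tempting, and the article does not support them:
- **That the phase 1 intervals are too narrow.** No phase 1 interval is announced, and a design effect does not move a percentage. Step 4 applies only if intervals are reported.
- **That factors will be falsely flagged at 11% each.** That rate needs a factor that varies only between associations. The listed items are personal attitudes and characteristics, and for these the excess is small.
- **That spurious factors will therefore enter the programme.** No significance rule selects its content. Expert input is combined with the survey findings, and the components already listed are not tied to regression coefficients.

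Purposive selection is a separate matter. It limits how far the estimates reach beyond the surveyed members, and clustered standard errors would not cure it.

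**Conclusion.** The point holds as a mismatch between design and named analysis. Phase 1 pays for a design effect of 1.5 and recruits through associations, yet nothing named in its analysis accounts for them. Run as written, and with the protocol's 1.5 taken as true, the standard error of a proportion is too small by a factor of 1.22. Regression tests run at about 5% to 7% for person-level factors, and at up to about 11% for a factor fixed within associations. The practical risk is that some influencing factors are flagged a little too readily.

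These sizes rest on the protocol's design effect being correct and arising from association membership, on assumed factor ICCs of 0 to 0.3, and on the approximation in step 5. A larger true design effect would make them worse, and a smaller one would shrink them. The issue concerns the survey and leaves its point percentages intact.

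**What to change.** State in the Plan for Data Analysis that the phase 1 logistic regression, and any confidence intervals reported for percentages, will account for welfare association. Either of these would do:
- standard errors clustered on association (GEE or a robust variance, with a small-sample correction if associations are few), or
- a random intercept for association.

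Report the ICC and the realised design effect, so that the assumed 1.5 can be checked.

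The cost is low. Each participant's association must be recorded. Phase 1 data collection was under way when the article was written, so this should be confirmed now. Intervals for percentages widen by about 22% if the design effect is 1.5, and less for coefficients of person-level factors. The sample size does not change, because 554 already allows for this.

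### Phase 2 is sized as a cluster randomised trial, but the effectiveness tests it names take no account of clustering in their standard use; at the plan's own design effect, a 5% test would run at about 11%

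*Protocol article*

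**What the plan says.** Under Research Design the article states that "phase 2 is a cluster randomized control trial". The Data Collection Plan repeats this: "In phase 2, cluster randomization will be used to select older adults for the experimental or control groups". Under Recruitment the sample is to be "randomly allocated to experimental and control groups from various welfare organizations of the Udupi district", which suggests that welfare organisations are the clusters. That is an inference, since no section names the unit of randomisation or gives the number or size of clusters.

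The Sample Size section allows for clustering in phase 2. It reports that "an initial sample size of 31 participants was calculated for each group", then "This initial size was adjusted by a design effect of 1.5", "yielding a total required sample size of 46 participants per group, rounded up to 50 participants per group".

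The Plan for Data Analysis lists the methods for judging the programme: "These tests include repeated measures ANOVA, 2-tailed *t* test, Mann-Whitney *U* test, Wilcoxon signed rank test", followed by chi-square. Nowhere does the article mention a random cluster effect, generalised estimating equations, cluster-robust errors, cluster-level summaries or an intracluster correlation (ICC).

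**The concern.** A design effect above 1 is the plan's own statement that participants in a cluster resemble each other. Clustering is therefore admitted when the trial is sized, yet no listed analysis uses it. Repeated measures ANOVA and the signed rank test deal with the correlation between a person's before and after scores. They do not deal with the correlation between different people in the same cluster.

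If the tests are run on individuals, standard errors are too small and the between-arm comparison does not hold its nominal level. The comparison with the control arm is the only controlled evidence on the programme, and the Conclusions foresee recommending it to welfare departments if testing succeeds. An inflated false-positive rate bears directly on that recommendation.

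**Working it through.** **Inputs.** Design effect (DE) 1.5, 31 per group before inflation, 46 after it, rounded to 50 (all Sample Size). A two-sided 5% level is assumed: the article gives no significance level and mentions two tails only for the t test.

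**1. The plan's own figure.** 31 × 1.5 = 46.5, against 46 stated. Phase 1 behaves the same way: 369 × 1.5 = 553.5, against 554. The design effect is thus applied to the sample size as described. The starting value of 31 cannot be rebuilt, because the two proportions, the level and the power are not given. The error rates below do not depend on it.

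**2. Type I error when clustering is ignored.** The true variance of the arm difference is DE times the variance that the test assumes, so

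true error = 2 × [1 − Φ(1.96 / √DE)], ratio of nominal to correct interval width = 1 / √DE, coverage = 1 − true error.

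At DE = 1.5: 1.96 / √1.5 = 1.600, so the error is 2 × [1 − Φ(1.600)] = 0.1095.

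| DE | True two-sided error | Width ratio | Coverage of nominal 95% interval |
|---|---|---|---|
| 1.2 (assumed) | 7.4% | 0.913 | 92.6% |
| **1.5 (plan)** | **11.0%** | **0.816** | **89.0%** |
| 2.0 (assumed) | 16.6% | 0.707 | 83.4% |

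At DE = 1.5, 50 participants carry the information of 50 / 1.5 = 33 independent ones.

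**3. Check by simulation.** There were 50 per arm, no true effect and a normal outcome, with 20,000 simulated trials (5,000 for Mann-Whitney). Cluster sizes m are assumed, and the ICC is set so that 1 + (m − 1) × ICC = 1.5, that is ICC = 0.5 / (m − 1).

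| Clusters per arm × size | ICC | t test | Mann-Whitney | Chi-square | t test on cluster means |
|---|---|---|---|---|---|
| 10 × 5 | 0.125 | 10.9% | 10.3% | 9.7% | 4.9% |
| 5 × 10 | 0.056 | 11.2% | 11.0% | 9.6% | 5.1% |
| 2 × 25 | 0.021 | 10.7% | 10.9% | 9.8% | 4.7% |

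For chi-square the simulated outcome was split at its mean after the ICC had been set on the continuous scale. This column matters because phase 2 was sized on two proportions. The individual-level tests agree with the formula to within about 1.5 percentage points, and the analysis of cluster means holds its level.

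**The case against.** The strongest reply is that this is a condensed article, that its list of tests is introduced as inclusive and not exhaustive, and that it never states the unit of analysis. A t test or Mann-Whitney test on cluster summaries would be valid, and model details often go into a separate analysis plan. This has some force: a reader might infer that every listed test is invalid and that p-values are bound to be too small, and the text does not go that far. What stands is that the article did not leave the analysis open. It named five methods, all of which ignore clustering in ordinary use, and stated no cluster-level use.

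Other limits also stand:

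- **Unit of randomisation.** Recruitment and the Data Collection Plan speak of cluster randomisation as a way to select people, which could describe cluster sampling followed by individual allocation. In that case the inflation would not apply in this form, and the design description and design effect would need correcting instead.
- **Larger error rates.** A reader might infer rates of 15% to 30% by assuming larger correlations. For example, clusters of 10 with ICC 0.10 give DE = 1 + 9 × 0.10 = 1.9, and clusters of 25 with ICC 0.10 give 1 + 24 × 0.10 = 3.4. The plan's own value is 1.5, and nothing in the article supports these higher ones. Smaller correlations are equally possible: clusters of 10 with ICC 0.02 give 1 + 9 × 0.02 = 1.18 and an error of about 7%.
- **Source of the correlation.** A reader might infer that it comes from teaching the sessions organisation by organisation. The programme description does not say so.
- **Signed rank test.** This is a before-after comparison, so the between-arm error rate does not describe it.

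The reply that the enlarged sample already handles clustering fails. Inflating the sample restores the power of an analysis that accounts for clusters. It does not correct the standard error of one that does not.

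**Conclusion.** The concern holds in this form: the analysis named for phase 2 does not match the design stated for it, and no section repairs the mismatch. If the listed tests are run on individuals, the between-arm type I error is about 11% in place of 5%, and nominal 95% intervals are about 18% too narrow, with about 89% coverage. This rests on the plan's design effect of 1.5, an assumed two-sided 5% level, clusters as the unit of randomisation, and a positive ICC for the analysed outcome, which the design effect presumes. Baseline adjustment may lower that ICC. Over design effects of 1.2 to 2.0 the error runs from 7.4% to 16.6%. The exact value cannot be fixed, because the number and size of clusters and the ICC are not given. The mismatch should be resolved before phase 2 is analysed, and preferably before it starts.

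**What to change.** In the Plan for Data Analysis, name one primary phase 2 analysis that uses the randomised cluster and adjusts for baseline. Two options are suitable:

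- a linear or logistic mixed model of the post-programme outcome, with arm and baseline value as fixed effects, a random intercept for cluster and a small-sample correction (for example Kenward-Roger for the linear model, or a t reference with between-cluster degrees of freedom);
- a t test on baseline-adjusted cluster means.

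State the unit of randomisation and the planned number of clusters, record the cluster identifier for each participant, and report the ICC. If individuals are in fact to be allocated within organisations, correct the design description and the design effect instead.

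**Cost.** No new outcome data are needed. Intervals will be wider, and correctly so. With few clusters the loss is larger: a test on cluster means with k clusters per arm has 2k − 2 degrees of freedom. Two clusters per arm leave 2 degrees of freedom and a critical value of 4.30, against about 1.98 for 100 independent individuals. Power would then be low, and more clusters might be needed. The number of clusters should therefore be settled together with the analysis.
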